### Sample size calculation

Being aware of the controversy whether RCT and efficacy studies reach the same effect sizes we used two recent meta-analyses on RCTs in STPP to estimate expected effect sizes. Abbass et al. (2006) [22] included trials on STPP with the majority of them (8 out of 13) not reporting manualized treatments. This condition comes closest to our comparison group receiving standard psychodynamic treatment. For general psychiatric symptoms effect sizes were medium (short term outcome d = .42, long term outcome d = .51). Based on the fact that effect sizes for specific target problems are usually larger, both treatment conditions will be expected to be superior to treatment as usual or no treatment. Both treatments seem to be highly acceptable and detrimental effects are not expected.

In their meta-analysis, Leichsenring et al. (2004) [23] reported effect sizes (prae-post) of d = .90 for the reduction of general psychiatric symptoms by STPP based on strictly manualized treatments. Compared to the results of Abbass et al. (2006) [22] with mostly non-manualized STPP we expect the between group effect size to be medium (about d = .48). Therefore, we pragmatically expected an effect size of 0.50 between the two groups (trained versus non trained therapist). In order to detect this difference at alpha = .05 (one-tailed) with a power of 0.80, N = 42 (one-tailed) patients per group are required according to the formula of Campbell et al. (2001) [24] for Cluster-Randomization, given that an average of 2 patients per therapist will be treated:

(z_α _= z-value for probability of error type I alpha, z_β _= z-value for probability of error type II beta, σ = standard deviation of outcome, E = expected ES of outcome, m = mean observations for each cluster, ρ = Intracluster correlation coefficient (ICC), ES = E/σ = standardized effect size)

While planning this study no meaningful published data on remission rates for manualized vs. non-manualized psychodynamic psychotherapy of social anxiety disorders were available. We based sample size calculation on available meta-analyses on psychodynamic psychotherapy all based on continuous outcomes. Estimating the sample size needed for a dichotomous approach (remission rates), we introduced the following conservative assumptions:

a) The ICC was set to 15%, which is high for comparable studies. According to Campbell (2001) [24] the ICC for outcome variables could be assumed to be less than 5%.

b) The average number of patients in a cluster was assumed to be 2. In fact, due to the prevalence of the disease we expect the average number of patients in a cluster to be less than 2.

c) Within the planning the sample size of 42 per group was calculated for patients completing the trial. For the primary analysis (ITT) drop-outs will be analysed as patients without remission. When assuming less than 50% remitters and an equal drop-out rate in both treatment groups, the absolute difference between remission rates will not change, but the relative difference will be much greater and will enlarge the difference between treatments substantially.

At a conservative drop-out rate of 25% (taking into account slightly elevated drop-outs in a practice study), a total of N = 105 patients are required to be allocated to the trial. Thus, N = 35 patients will have to be included in each centre. According to the data of the Davidson et al. (2004) [25] study with social phobia patients, N = 257 patients would have to be assessed for eligibility. As all patients have already received a clinical diagnosis by the practitioner before undergoing the standardized interview, we estimate that not more than about 250 patients will have to be assessed for eligibility.

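### The two meta-analytic effects cited in the Sample size calculation do not support a between-group d of about .48, or the 0.50 planned from it

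*Protocol article*

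**What the plan says.** All the relevant text is in the Protocol article, Methods/Design, Sample size calculation.

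- Source of the planning effect: "we used two recent meta-analyses on RCTs in STPP to estimate expected effect sizes".
- The meta-analysis taken as closest to the control condition: "For general psychiatric symptoms effect sizes were medium (short term outcome d = .42, long term outcome d = .51". Eight of its 13 trials did not report a manual.
- The meta-analysis taken to represent the trained condition: it "reported effect sizes (prae-post) of d = .90 for the reduction of general psychiatric symptoms by STPP based on strictly manualized treatments".
- The step from these two to the trial contrast: "with mostly non-manualized STPP we expect the between group effect size to be medium (about d = .48".
- The planning value: "Therefore, we pragmatically expected an effect size of 0.50 between the two groups (trained versus non trained therapist".

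With one-tailed alpha .05, power .80, two patients per therapist and an ICC of 15%, the section arrives at 42 completers per group. It offers no other basis for .48 or 0.50.

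**The concern.** The trial compares patients of trained therapists with patients of untrained therapists, so the planning effect must be a difference between two therapies. The article builds it from two numbers that do not appear to measure the same thing.

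A pre-post effect is the change within treated patients. It includes natural course and regression to the mean as well as any effect of therapy. An effect against controls has that background change removed. Subtracting the second from the first leaves the background change in the answer.

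Only .90 carries the pre-post label. The .42 comes from a meta-analysis of RCTs, has no such label, and is followed by the statement that "both treatment conditions will be expected to be superior to treatment as usual or no treatment". That reads most naturally as an effect against controls.

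The planning effect is the main input to the 42 per group and the claimed 80% power. If the cited evidence does not support it, the reader is told that the trial is well powered for an effect the literature predicts, when 0.50 is in fact only an assumption.

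**Working it through.** **Inputs (Sample size calculation).** Pre-post d = .90 (manualized); d = .42 short term and .51 long term (mostly non-manualized); planning d = 0.50; one-sided alpha .05; power .80; m = 2 patients per therapist; ICC = .15; 42 completers per group.

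**Step 1: reproduce the effect size.** .90 - .42 = .48. The article does not write the subtraction out, but the result matches exactly. With the long-term figure, .90 - .51 = .39. The short-term figure is the more natural match to a primary endpoint after 25 sessions, so .39 only shows how much the result depends on which cited number is used.

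**Step 2: what the difference estimates.** Let T_m and T_n be the pre-post effects of manualized and non-manualized therapy, and C the pre-post change in the controls behind the second meta-analysis. Assume for simplicity that all are scaled by the same standard deviation.

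- If .42 is an effect against controls, .42 = T_n - C. Then .90 - .42 = T_m - T_n + C, which is the wanted contrast plus C. The documents give no value for C. Pre-post and controlled effects may also be standardized differently, so even this identity is approximate.
- If .42 is also pre-post, C drops out and .90 - .42 = T_m - T_n. The two terms still come from separate sets of trials, with no common comparator and no adjustment. Both concern general psychiatric symptoms, not the LSAS. Up to 13 - 8 = 5 of the trials behind .42 may have used a manual.

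Neither reading gives a supported estimate of trained versus untrained therapists.

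**Step 3: reproduce the 42.** n per group = 2(z_alpha + z_beta)²/d² × [1 + (m - 1) × ICC].
At d = .50: 2(1.645 + 0.842)²/.25 = 49.5, and 49.5 × 1.15 = 56.9, so 57. The stated 42 does not follow from the stated inputs; without clustering the answer is already 50. This is a separate error, and correcting it would leave the effect size just as unsupported.

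**Step 4: power at the fixed 42 per group.** Power = Φ(d × √(42/(2 × 1.15)) - 1.645) = Φ(4.273d - 1.645). Except for .50, .48 and .39, the values of d are illustrative and not from the documents.

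| Assumed d | Power with 42 per group | Completers per group for 80% |
|---|---|---|
| .50 | 69% | 57 |
| .48 | 66% | 62 |
| .40 | 53% | 89 |
| .39 | 51% | 94 |
| .30 | 36% | 158 |
| .20 | 22% | 356 |

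The effect detectable with 80% power is 2.487/4.273 = .58.

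These figures are for a continuous outcome, the scale on which the article plans. The primary test is on binary remission (LSAS ≤30), so they are not the power of that test.

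**The case against.** The strongest reply is that the article never says what kind of effect .42 is. The sentence on superiority rests on a different premise, that effects on target problems tend to be larger, and it covers both treatments, including the one matched to .90. The controlled reading is therefore an inference, and the source that would settle it is not available here. This stands: a reader might take the mixing of two kinds of effect as established, and the documents do not go that far. The conclusion does not need it, because the other reading also fails to give a between-therapy effect.

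Second, the article is partly candid. It reports that eight of 13 trials lacked a manual, names the outcome as general symptoms, uses hedged wording and says that remission data were lacking. This stands in part. The admission about missing data concerns remission rates, and the word for pragmatic covers only the small step from .48 to 0.50. The .48 itself is still presented as what the two sources imply.

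Third, a reader might infer that the true effect must be below 0.50. The documents do not support that. The change in controls is not given. The article's point about target problems could push the LSAS difference upward. So could manualized trials within the .42, if manuals raise effects. An unsupported figure is not thereby shown to be too large.

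Last, a reader might blame this input for the whole loss of power. At d = .50, the fall from 80% to 69% comes entirely from 42 being used where the stated inputs give 57.

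**Conclusion.** The point holds in a limited form. The expected d of about .48 is recovered only as .90 - .42, and on either reading of .42 this is not a usable estimate of the effect of training therapists. The cited meta-analyses do not support .48 or 0.50. That .42 is an effect against controls is the likelier reading but remains an inference.

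The consequence is uncertainty about power, not a demonstrated overstatement of the effect. Over an assumed range of d from .50 down to .20, continuous-scale power at 42 per group runs from about 69% to 22%. This rests on the plan's one-sided .05, two patients per therapist and ICC .15, and on a normal approximation. There is no single corrected sample size, because the documents contain no like-for-like effect from which to compute one.

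**What to change.** In the Sample size calculation:

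1. Remove the statement that the two meta-analyses lead to a between-group d of about .48, and the inference from it to 0.50.
2. State that 0.50 is an assumed target difference between trained and untrained therapists, chosen without direct evidence.
3. Beside the fixed sample size, print the power at 42 per group with one-sided .05, m = 2 and ICC .15: about 69% at d = .50, 53% at .40, 36% at .30 and 22% at .20, with d of about .58 detectable at 80% power. Label these as continuous-scale figures.
4. Note that the gap between 80% and 69% at d = .50 comes from the sample size formula (57 per group, not 42) and is to be corrected as a separate matter.

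The cost is a rewording of one section and a less favourable power statement. This change requires no additional patients and alters neither the endpoint nor the analysis.

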#### Secondary analyses

Self-report questionnaires and observer ratings (SPAI, CGI, BDI, FSKN, DKB-35, CDS, BSSS, EQ-5D, HAQ, treatment adherence) will be analysed by mixed models with repeated measurements. Further analyses will include

• cross-sectional analyses comparing therapists;

• subgroup analyses of subjects' and therapists' conditions

• costs of the SP treatment (CSSRI)

All analyses will be conducted on a one-sided level of significance of 0.05. Descriptive statistics showing the measurements over time will be presented whenever appropriate.

Serious adverse events and drop-outs will be analysed descriptively.

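### The sample size of 42 per group does not follow from the stated inputs: they require 57 per group, and 42 gives about 69% power at one-sided 0.05

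*Protocol article*

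**What the plan says.** All the inputs are in the protocol article.

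- **Effect, under Sample size calculation:** "we pragmatically expected an effect size of 0.50 between the two groups".
- **Error rates, same section:** "In order to detect this difference at alpha = .05 (one-tailed) with a power of 0.80". The subsection on secondary analyses confirms the level: "All analyses will be conducted on a one-sided level of significance of 0.05".
- **Clustering:** the formula is applied "given that an average of 2 patients per therapist will be treated", and "The ICC was set to 15%, which is high for comparable studies". The section calls both values conservative.
- **Result:** "with a power of 0.80, N = 42 (one-tailed) patients per group are required". The same section says the 42 are patients who complete the trial. The totals of 84 completers, 105 enrolled and 35 per centre are built on it.

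The section lists the symbols of the formula (the two z-values, σ, E, m, ρ and ES = E/σ). The displayed formula itself is lost from the text available for review.

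**The concern.** A quick check without clustering already gives a larger number than the protocol reports. Detecting half a standard deviation at one-sided 0.05 with 80% power takes about 50 patients per group when observations are independent. A cluster adjustment with positive ICC can only raise that. A cluster-adjusted 42 therefore cannot be right at the stated level and power.

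This is the only power justification in the article. If it is wrong, the chance of missing the planned effect is larger than the 20% readers will assume. A non-significant result on therapist training would then be read as coming from a trial with 80% power when it did not have it.

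**Working it through.** **Inputs, all as stated:** ES = 0.50; one-sided alpha 0.05 (z = 1.645); power 0.80 (z = 0.842); m = 2; ρ = 0.15; equal groups.

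**Formula.** Using the symbols the section defines, the standard form for comparing two means under cluster randomization is

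n per group = 2(z_α + z_β)² / ES² × [1 + (m − 1)ρ].

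The design effect is 1 + (2 − 1) × 0.15 = 1.15.

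**1. Trying to reproduce 42**

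| Setting | Before rounding | n per group |
|---|---|---|
| As stated: one-sided 0.05, ES 0.50, ICC 0.15 | 49.46 × 1.15 = 56.88 | 57 |
| ICC 0.05 | 49.46 × 1.05 = 51.93 | 52 |
| No clustering | 49.46 | 50 |
| Two-sided 0.05, ICC 0.15 | 62.79 × 1.15 = 72.21 | 73 |
| ES 0.48 (the value before rounding to 0.50), ICC 0.15 | 53.67 × 1.15 = 61.72 | 62 |
| One-sided 0.10, otherwise as stated | 36.06 × 1.15 = 41.47 | 42 |

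The first row is 2 × (1.645 + 0.842)² / 0.25 × 1.15. The last is 2 × (1.282 + 0.842)² / 0.25 × 1.15. No valid setting at alpha 0.05 gives 42. Dividing by the design effect instead of multiplying gives 49.46 / 1.15 = 43.01, which is close to 42 but is not a legitimate use of the factor.

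**2. Power with 42 per group at one-sided 0.05**

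The effective size is 42 / 1.15 = 36.52 per group. The standardized shift is 0.50 × √(36.52 / 2) = 2.137.

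Power = Φ(2.137 − 1.645) = 0.689. A calculation with the t distribution gives 0.68.

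- With ICC 0.05, power is 0.723.
- With ICC 0, power is 0.741.
- At one-sided alpha 0.10 with ICC 0.15, Φ(2.137 − 1.282) = 0.804. So 42 would have been adequate at that level.

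**3. Effect detectable with 80% power at 42 per group**

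ES = √(2 × 6.183 × 1.15 / 42) = 0.58.

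**4. Completers needed for the stated power**

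2 × 57 = 114, against 84 planned. That is 30 more, or 36%. At 57 per group the power is 80.1% by the same formula.

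**The case against.** Four points can be made for the plan.

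- **The clustering assumptions are conservative.** The section expects a true ICC below 5% and fewer than two patients per therapist. This does not help enough: with clustering removed altogether, 50 per group are needed and 42 gives 74%.
- **The intention-to-treat analysis uses all 105 patients.** With 52.5 per group, ICC 0.15 and an undiluted effect of 0.50, power is still only 77%. Counting drop-outs as non-remitters would not leave the effect undiluted.
- **The cause is not proven.** This stands. Because the displayed formula cannot be seen, the use of the z-value for one-sided 0.10 is an inference from the exact match at 42. The discrepancy itself does not depend on how it arose.
- **The 69% is not the power of the primary test.** This also stands. It is the corrected output of the plan's own calculation, for a continuous outcome in completers. The primary test compares remission rates with drop-outs counted as failures. Its power depends on how an effect of 0.50 is translated into remission rates. Assume control remission of 20–40%. Reading 0.50 as an arcsine difference among 42 completers per group gives 68–69%. Converting it to an odds ratio of 2.48, with 52.5 per group, design effect 1.15 and 20–25% drop-outs counted as non-remitters, gives about 48–55%. Neither reading reaches 80%.

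**Conclusion.** The point holds. The stated inputs give 57 per group, not 42. With 42 completers per group the plan's own calculation has 69% power (74% with no clustering at all), so the risk of missing an effect of 0.50 is about 31% rather than 20%. Power of 80% is reached at 0.58.

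The result rests on the standard cluster formula built from the symbols the section defines, and on the protocol's own values. It needs no outside figure, and no ICC or cluster size reverses it. It must be corrected because it is the primary power statement and all recruitment targets derive from it.

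**What to change.** In the sample size section:

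1. Replace 42 by 57 per group (114 completers) as the number required for an effect of 0.50 at one-sided 0.05 with 80% power, m = 2 and ICC 0.15.
2. If 42 per group stays as the planned number, say so. State that it gives about 69% power for 0.50, and 80% power for 0.58, in the continuous calculation among completers. Add that this is not the power of the intention-to-treat remission test. Any reason for staying at 42 should be the investigators' actual one; the article gives none beyond the calculation.
3. Do not move the test level to one-sided 0.10 to make 42 fit. The sample size section and the analysis section both fix 0.05.

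Restating the figures costs wording and a less favourable stated power, with no extra patients. Keeping the 80% target instead would mean 30 more completers.

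While the section is open, the drop-out step needs a separate look. The figure of 105 is 84 × 1.25, whereas 25% drop-out calls for 84 / 0.75 = 112 (or 114 / 0.75 = 152 if the 80% target is kept). Correcting 42 alone does not repair that step.

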### Participants

Patients' inclusion and exclusion criteria are listed in table 1. According to these criteria, the sample of patients included in the study is representative for patients suffering from social phobia who qualify for treatment in an outpatient setting. No subject will be allowed to enrol in this trial more than once. Over a period of three years, a total of 105 patients are planned to be enrolled in the study (35 patients in each centre). A minimum number of 84 completers is intended.

**Table 1 T1:** Inclusion and exclusion criteria

Inclusion criteria	Diagnosis of SP (SCID-I [8]) and Liebowitz Social Anxiety Scale >30 (>60 for generalized subtype) [9] age: 18 to 70 years SP must be primary diagnosis (most severe disorder according to ADIS-IV) SP patients with comorbid disorders will be included, provided that SP is the primary diagnosis, thus ensuring a clinically representative sample as well as analyses of subgroups (e.g. type of SP, patients with comorbid depressive disorder) Informed consent.
**Exclusion criteria**	psychotic disorder prominent risk of self-harm acute substance related disorders personality disorders except for cluster C: avoidant, obsessive-compulsive or dependent personality disorder (SCID-II) organic mental disorder severe medical conditions concurrent psychotherapeutic treatment psychopharmacological treatment (stable medical treatments; e.g. SSRI without dose adaptation are permitted)

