### Statistical analysis

#### Primary analysis

The following hypothesis will be tested:

H_0_: π_manualized _≤ π_standard _vs. H_1_: π_manualized _> π_standard_

where π_manualized _and π_standard usual _are the true remission probabilities in the manualized treatment group and the standard routine care group after treatment period respectively.

Remission rates will be compared between specifically trained STPP (manualized) and psychodynamic treatment as usual (standard) group by logistic regression with covariates for treatment, sex of the therapist, and experience of the therapist. Due to the cluster randomized nature of the study a term for the therapist will be added. Within each therapist compound symmetry will be assumed. Intent-to-treat analyses (LOCF) as well as completer analyses will be conducted. Drop-outs will be considered as non-responders/non-remitters in the analysis. As sensitivity analyses a chi-square test and a conditional logistic regression adjusted for the therapist will be performed. Also the LSAS will be analysed as a continuous measure by means of mixed model with repeated measurements for the ITT population. Replacement strategies of missing values will be discussed after assessing the pattern of the missing value structure.

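### Counting equal drop-out as non-remission shrinks the absolute difference and leaves the risk ratio unchanged, so assumption (c) is wrong on both counts and is not conservative

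*Protocol article*

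**What the plan says.** In the protocol article, "Sample size calculation" lists three assumptions that it calls conservative, meant to carry a calculation for a continuous effect size over to remission rates. The third, item (c), makes these statements:

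- The basis is completers: "the sample size of 42 per group was calculated for patients completing the trial".
- The drop-out rule is: "For the primary analysis (ITT) drop-outs will be analysed as patients without remission". "Primary analysis" repeats it: "Drop-outs will be considered as non-responders/non-remitters in the analysis".
- The conditions are: "When assuming less than 50% remitters and an equal drop-out rate in both treatment groups".
- The stated consequence is: "the absolute difference between remission rates will not change, but the relative difference will be much greater". The sentence goes on to say that this substantially widens the treatment difference.

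The same section then sets the inflation, "At a conservative drop-out rate of 25" (per cent), and concludes that "a total of N = 105 patients are required to be allocated to the trial". "Participants" adds: "A minimum number of 84 completers is intended". The test itself is a one-sided logistic regression of remission.

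**The concern.** Item (c) is the only argument the article gives for using a completer-based number in an ITT primary analysis. It tells the reader that the drop-out rule costs nothing on the absolute scale and gains on the relative scale, so that 42 completers per group is a safe figure. If the rule instead dilutes the effect, an assumption presented as a safety margin is a loss of power, and the 80% attached to the completer calculation cannot be read as ITT power.

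**Working it through.** **Inputs from the article.** 42 completers per group (84 in total); 105 enrolled, so 52.5 per group; drop-out stated as 25%; one-sided alpha 0.05; ICC 0.15 and 2 patients per therapist, so the design effect is 1 + (2−1)×0.15 = 1.15.

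**Inputs assumed.** The article says that no meaningful remission data were available and gives no rates. The pairs below are illustrations only, all under 50% to respect the condition in (c). The design effect is held at 1.15 in both populations.

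**The plan's own figures.**

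- 84 × 1.25 = 105, but (105 − 84)/105 = 20%. The stated rate and the counts therefore describe two different drop-out rates. At a true 25%, 42 completers need 42/0.75 = 56 enrolled per group.
- The 42 per group does not reproduce from the stated inputs: 2 × (1.645 + 0.842)² / 0.50² × 1.15 = 56.9. That is a separate matter. Here 42 is taken as given.

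**Step 1: effect measures.** Let the completer remission rates be p₁ and p₂, with the same drop-out rate w in both groups and all drop-outs counted as non-remitters.

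- ITT rates: (1−w)p₁ and (1−w)p₂.
- Absolute difference: (1−w)(p₁ − p₂). It is multiplied by 0.75 at w = 25% and by 0.80 at w = 20%.
- Risk ratio: (1−w)p₁ / (1−w)p₂ = p₁/p₂, unchanged.
- Odds ratio: moves toward 1.

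Example, 40% vs 20%:

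- At w = 25% the rates become 30% vs 15%: difference 20 to 15 points, risk ratio 2.00 to 2.00, odds ratio 2.67 to 2.43.
- At w = 20% they become 32% vs 16%: difference 16 points, risk ratio 2.00, odds ratio 2.47.

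The under-50% condition plays no part in this algebra.

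**Step 2: does the larger ITT denominator make up for it?** With n completers per group and n/(1−w) enrolled, the standardised differences are

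- completers: z = (p₁ − p₂) / √{[p₁(1−p₁) + p₂(1−p₂)] × 1.15/n}
- ITT: z = (p₁ − p₂) / √{[p₁(1−(1−w)p₁) + p₂(1−(1−w)p₂)] × 1.15/n}

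The second follows by cancelling (1−w) above and below. Since 1−(1−w)p exceeds 1−p whenever w and p are above zero, the ITT z is always the smaller.

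**Step 3: size.** Power = Φ(z − 1.645). For 40% vs 20%:

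- Completers: 0.20/√(0.40 × 1.15/42) = 1.911, power 60.5%.
- ITT, w = 20%, 52.5 per group: 0.16/√(0.352 × 1.15/52.5) = 1.822, power 57.0%.
- ITT, w = 25%, 56 per group: 0.15/√(0.3375 × 1.15/56) = 1.802, power 56.2%.

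The same formulas for all pairs:

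| Assumed completer rates | Completers, 42 per group | ITT, 20%, 52.5 per group | ITT, 25%, 56 per group |
|---|---|---|---|
| 10% vs 25% | 53.0% | 51.3% | 50.9% |
| 15% vs 30% | 46.6% | 44.7% | 44.2% |
| 20% vs 40% | 60.5% | 57.0% | 56.2% |
| 25% vs 49% | 70.8% | 65.9% | 64.8% |

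The losses are 1.7 to 4.9 points at 20% and 2.1 to 6.0 points at 25%.

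**The case against.** Several defences of the sentence deserve a hearing.

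- **The variance argument.** If the absolute difference really were preserved while both rates fell from below 50%, the ratio would rise and the variance would fall. The reasoning is coherent given its premise, but the premise fails: equal drop-out removes the same proportion from each rate, not the same number of points. The variance does fall (0.40 to 0.352 in the example at 20%), and that is why the loss is modest, but it does not close the gap.
- **Counts of remitters.** Read as a difference in the number of remitters, the first half survives, since drop-outs add none. The claim of a much greater relative difference still fails.
- **Last observation carried forward.** "Primary analysis" also names this for the ITT analysis, and it could classify some drop-outs differently. Both sections nevertheless say that drop-outs are non-remitters, and item (c) argues from that rule.
- **No number depends on the sentence.** This stands. The 42 comes from d = 0.50 and the 105 from 84 × 1.25. Correcting the sentence changes no enrolment figure, endpoint or analysis.

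A reader might also infer more than the article supports:

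- *That the claim is exactly reversed.* It is not. The article says unchanged and greater; the truth is smaller and unchanged. Each statement is wrong, but they are not swapped.
- *That the power loss is about 8 points.* Setting 42 completers against 52.5 ITT patients diluted by 25% gives that sort of figure (55.5% to 47.6% for 30% vs 50%). But 52.5 × 0.75 = 39.4, not 42, so the comparison mixes two drop-out rates and counts the 1.25 inflation as part of the dilution. The 50% arm also lies outside the article's own condition.
- *That powers near 50% to 70% are caused by item (c).* They come from the assumed rates and from the 42.

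**Conclusion.** The point holds. Under its own conditions, item (c) is wrong about both the absolute and the relative difference, at any remission rate. The absolute difference falls by a quarter at the stated drop-out rate, or by a fifth on the counts. The risk ratio is unchanged, and the odds ratio, the scale of the primary logistic model, shrinks. These results need only equal drop-out and drop-outs counted as failures.

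The rule is therefore not conservative for the ITT analysis, and ITT power lies below completer power. The size of that loss rests on assumed rates, a design effect of 1.15 in both populations and a simple comparison of two proportions. It is about 2 to 6 points over the pairs shown when the drop-out rate and the counts are kept consistent. What the article loses is its stated bridge from completers to ITT, not a computed number.

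**What to change.** Replace the sentence in item (c) with: *With equal drop-out w, counting drop-outs as non-remitters multiplies the absolute difference by (1−w) and leaves the risk ratio unchanged, so ITT power is lower than completer power.*

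Remove (c) from the list of conservative assumptions. State the ITT power on the diluted rates, over a range of remission rates labelled as assumed, using one drop-out rate that agrees with the counts (20% with 105 enrolled, or 25% with 56 per group, 112 in all).

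The cost is one corrected sentence and one short power table. This correction requires no change to enrolment, but the stated power becomes less favourable.

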**Methods/Design:**

The manualized treatment is designed for a time limited approach with 25 individual sessions of STPP over 6 months. Private practitioners will be randomized to training in manualized STPP vs. treatment as usual without a specific training (control condition). We plan to enrol a total of 105 patients (84 completers). Assessments will be conducted before treatment starts, after 8 and 15 weeks, after 25 treatment sessions, at the end of treatment, 6 months and 12 months after termination of treatment. The primary outcome measure is the Liebowitz Social Anxiety Scale. Remission from social phobia is defined scoring with 30 or less points on this scale.

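### The drop-out inflation is wrong: 105 patients at 25% drop-out leave about 79 completers, not the 84 the plan requires

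*Protocol article*

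**What the plan says.** The Sample size calculation section derives 42 patients per group and makes clear that these are completers: "Within the planning the sample size of 42 per group was calculated for patients completing the trial". It then allows for attrition and gives the number to be allocated: "At a conservative drop-out rate of 25% (taking into account slightly elevated drop-outs in a practice study), a total of N = 105 patients". The centre targets follow from that total: "Thus, N = 35 patients will have to be included in each centre".

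The same pair of totals appears in two other places. The Methods/Design part of the abstract says "We plan to enrol a total of 105 patients (84 completers"). The Participants section says "A minimum number of 84 completers is intended".

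**The concern.** A drop-out rate is normally a share of the patients who enter the trial. On that meaning, enrolment, drop-out rate and number of completers are tied together: any two fix the third. Here all three are stated, and they do not fit.

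At stake is whether the trial can reach its own target. The plan calls 25% conservative and justifies it by the practice setting. If that rate occurs, the trial falls below its stated minimum of completers even when every centre recruits in full. The error sits in the headline enrolment figure and carries through to the target for each centre.

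**Working it through.** **Inputs, all from the protocol article**

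- Completers needed: 42 per group, 84 in total (Sample size calculation; Participants; abstract).
- Drop-out rate: 25% (Sample size calculation).
- Enrolment: 105, or 35 in each of three centres (Sample size calculation; Participants; abstract).
- For power: d = 0.50, one-sided alpha 0.05, 2 patients per therapist, ICC 0.15 (Sample size calculation).

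**Reproducing the plan's figure**

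- Completers x (1 + drop-out) = 84 x 1.25 = 105. This matches exactly, and 105/3 = 35 per centre.

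**The correct inflation**

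- Enrolment = completers / (1 - drop-out) = 84/0.75 = 112.
- Per group: 42/0.75 = 56, again 112 in total.
- The stated figure is 112 - 105 = 7 patients too low.

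**Reverse checks**

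- Completers expected from 105 at 25%: 105 x 0.75 = 78.75, about 79, or 39.4 per group if the groups are equal. Shortfall: 84 - 78.75 = 5.25, about 6% of 84.
- Drop-out rate implied by 105 and 84: 1 - 84/105 = 0.20, that is, 20%.

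**Effect on power**

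The article's sample size formula is not visible in the text, so I assume the usual design effect, 1 + (m - 1) x ICC = 1 + 1 x 0.15 = 1.15. With n completers per group,

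power = Φ( d x √( n / (2 x 1.15) ) - 1.645 ).

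| Completers per group | d x √(n/2.30) | minus 1.645 | Power |
|---|---|---|---|
| 42 | 2.137 | 0.492 | 0.689 |
| 39.375 | 2.069 | 0.424 | 0.664 |

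The loss due to the drop-out step is about 2.5 percentage points. The 0.689 at 42 per group is already below the stated 0.80, but that gap has another cause. On the same assumptions the inputs give 2 x ((1.645 + 0.842)/0.50)² x 1.15 = 56.9, so 57 completers per group. It should not be counted against the drop-out step.

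**The case against.** The strongest reply concerns weight, not arithmetic. The primary analysis is by intention to treat and counts drop-outs as non-remitters, so all 105 patients stay in it. The completer count directly limits only the completer analysis. The power figures above are for a continuous outcome in completers, whereas the primary test compares remission proportions. An allowance for drop-out also exists: 105 covers a rate of up to 20%, and the shortfall appears only if drop-out exceeds that.

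Most of this stands as a statement of size. The margin is smaller than claimed, not absent. The power loss is small and is not the power of the primary test.

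It does not rescue the figure. The plan itself defines 42 per group as completers, inflates from that number and calls 84 a minimum. Nor does keeping drop-outs as non-remitters make up for losing them. With equal 25% drop-out in both groups, a difference in remission among completers is multiplied by 0.75. For illustration, with assumed rates of 50% and 30%, it becomes 37.5% against 22.5%, a difference of 15 points instead of 20.

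The figures would agree if 25% meant drop-outs per completer (21/84). That is not the ordinary meaning of a drop-out rate, and the text gives no sign of it. Rounding cannot explain a gap of 7 patients. Nor is this a detail left to a fuller document, since all three numbers are printed here.

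**Conclusion.** The concern holds. Enrolment of 105, drop-out of 25% and 84 completers are inconsistent, and nothing in the article reconciles them. The allowance actually built in is 20%. If 25% occurs, about 79 patients complete, some 5 (6%) below the stated minimum.

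The arithmetic needs no assumption beyond the usual meaning of a drop-out rate. The power loss of about 2.5 points rests on equal groups, a design effect of 1.15 and a continuous outcome in completers. The practical effect is modest, but a headline design figure does not follow from the plan's own inputs, and it should be corrected.

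**What to change.** Make the three figures agree in the abstract, Participants and Sample size calculation sections, in one of these ways:

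- **Keep 105 and 25%.** State that about 79 completers (39 to 40 per group) are expected, replace the minimum of 84, and give the power for that number. On the stated inputs and the design effect above, this is about 66% for the continuous comparison.
- **Keep 105 and 84.** State that the drop-out assumption is 20%, and no longer present 25% as the allowance.
- **Keep 84 and 25%.** Raise enrolment to 112, which is 37 or 38 patients per centre.

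The first two cost wording only. The third costs 7 more patients.

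The figure of 112 repairs the drop-out step alone. It does not deliver 80% power on the plan's stated inputs, because the 42 per group does not follow from them. That derivation needs its own correction, and the inflation should then be redone by dividing by one minus the drop-out rate.
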